**Fig 3 pone.0306408.g003:**
[figure not shown]
Example of sampling schedule. Above schedule assumes a wakefulness period of seventeen hours. Schedules are adjusted relative to individual rhythms. Participants are instructed to start sampling of hair follicles and saliva at awakening and every six hours hereafter, as well as one sample at bed time. Additional saliva samples are collected every two hours after twelve hours wakefulness and approximately one hour before bedtime. Oral temperature is measured concurrently with saliva sampling.

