#### At-home testing

For two consecutive days participants will sample saliva approximately six times (depended on wakefulness period) per day, hair samples four times per day and record body temperature and dietary food intake (S1 File). Participants are provided with an individualized schedule indicating all sampling times. Participants will collect saliva by a chewable saliva collector (Salivette Cortisol saliva collector, Sarstedt, Nümbrect, Germany). Saliva sampling entails placing one (or two in case of xerostomia, common with some psychotropic drug [28]) small moisture absorbing cottonous tube in the mouth which is then spat into a test tube and refrigerated. Participants are instructed to avoid food or drinks 30 minutes before saliva sampling, and to follow their normal meal times. Oral temperature are collected simultaneously with saliva sampling using an oral thermometer according to manufacturers’ instructions (Apotekets, Skovlunde, Denmark). Hair follicles are self-sampled with tweezers. Participants will pluck 20 hairs from the scalp or chin and place these in a date- and time marked tube containing dissolution buffer (RNeasy Micro Kit; QIAGEN, Hilden, Germany). Immediately after sampling, follicle- and saliva samples are placed in the refrigerator. If participants need to collect samples away from their home they are provided with cooling bags and icepacks.

During each of the two home-sampling days, participants are offered home visits from a study representative, a health professional trained in collecting hair follicles. If the participant declines this offer, telephone meetings are scheduled instead. If possible, home visits will be scheduled around a sampling time, during these visits the sample is collected by the study representative. This is to allow for comparison between self- and professional- sampling. During visits, additional data is gathered on light exposure and media device screen time usage (S4 File), and any potential safety concerns are noted and dealt with as applicable under the regulations for out-patient treatment.

#### Clinical visit 2

Following the two sampling days, participants will again meet at the clinic. Participants are asked to fill in the Morningness-Eveningness Questionnaire (MEQ) and a brief questionnaire on their experience on how easy/troublesome they found different aspects of sampling.

#### Clinical visit 3

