#### Statistical analyses

The four observational groups will be compared on group characteristics of e.g., BMI, body composition, physical function and SES using One-Way Analysis of Variance (ANOVA) or Kruskal-Wallis tests for continuous or ordinal outcomes, and Chi-squared statistics for categorical outcomes as dictated by model assumptions and applying suitable post-hoc analyses as appropriate.

The primary outcome will be analyzed for each study group. Rhythmicity will be assessed by approximating each individual’s 48-hour profiles to a 24 hour cosine wave function in non-linear mixed effects models thereby allowing for the estimation of amplitude, acrophase, and mesor for each group. Derived variables will be compared between groups using the non-obese control group as the reference. Inter-day variability of circadian parameters will be analyzed for each group. Cosine analyses will be individualized relative to participants objectively measured mean sleep offset time.

The same procedure will be used for the secondary measures of rhythmicity i.e. salivary cortisol and melatonin values. In addition, peak values and peak to trough values will be calculated and compared between groups. Wake-to-bed slopes of cortisol will be calculated by subtracting the bedtime sample value from the sample collected immediately upon awakening and divided by the number of hours separating these two samples [31]. Dim light melatonin onset (DLMO) is estimated by comparing evening melatonin concentrations to the mean levels obtained from samples collected during daylight hours. Other potentially rhythmic variables (blood glucose, oral pH and oral temperature) will be visually reviewed for rhythmicity and if applicable analyzed by similar methods.

The correlation between clock gene expression and sleep parameters (e.g., sleep quality, MEQ-category, AHI, and other sleep parameters (S5 File)) will be investigated through Spearman’s rho in correlation matrices. Additional potentially confounding variables will be added to these matrices. This includes variables related to diet, body composition, medication, physical activity and media device usage.

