Similarly, salivary sampling times in our study are chosen for participant compliance. Typically, cortisol samples are collected several times within the first hour after awakening to estimate the cortisol awakening response [31,47]. However, this would result in the participant having to postpone breakfast and would not align with a natural work rhythm. Similarly, for melatonin, we modified the standard Danish method of sampling every 30 minutes from a fixed evening time (e.g., 5 pm) until bedtime [48] to two-hour intervals to accommodate regular eating patterns, with an additional sample one hour before bedtime to enhance the accuracy of DLMO prediction.

Overall, the chosen sampling schedule for hair follicles and saliva are designed to capture major shifts in clock gene and hormonal rhythms due to circadian disruption or mental disease while disrupting daily habits as little as possible. This approach, while enhancing ecological validity of the study, introduces a significant degree of variability compared to more controlled clinical studies. To account for this variability, we are implementing measures to track and adjust for several confounding variables.

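### Melatonin peak, peak-to-trough and cosinor parameters are compared between groups although no saliva is taken during sleep, so they partly depend on when each participant goes to bed

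*Protocol article*

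**What the plan says.** The protocol article is the only document available.

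- **Sampling (Fig 3 caption, At-home testing).** Saliva is taken on awakening, at six-hour steps while awake, and at bedtime. The caption adds: "Additional saliva samples are collected every two hours after twelve hours wakefulness and approximately one hour before bedtime". It also states: "Above schedule assumes a wakefulness period of seventeen hours". At-home testing gives the count: "participants will sample saliva approximately six times (depended on wakefulness period) per day". No sample is planned during sleep.
- **Analysis (Statistical analyses).** Clock-gene profiles are fitted by a 24-hour cosine to give mesor, amplitude and acrophase, with time set relative to each participant's mean sleep offset. For the hormones: "The same procedure will be used for the secondary measures of rhythmicity i.e. salivary cortisol and melatonin values". Then: "In addition, peak values and peak to trough values will be calculated and compared between groups".
- **Other hormone measures (Statistical analyses).** A wake-to-bed cortisol slope is planned. Dim light melatonin onset (DLMO) is to be estimated by "comparing evening melatonin concentrations to the mean levels obtained from samples collected during daylight hours".
- **Status (Main outcomes).** Cortisol and melatonin rhythms are the secondary outcomes; clock-gene expression is primary.
- **Expected group difference (Strength and limitations).** Both psychiatric groups are expected to fall asleep later and sleep longer. No size is given.
- **Disclosed limits (Strength and limitations).** The article explains that saliva times were chosen for compliance, that evening melatonin sampling was thinned, and that the usual dense cortisol sampling after waking is not done: "Typically, cortisol samples are collected several times within the first hour after awakening to estimate the cortisol awakening response". It does not name the unsampled night as a limit on peak, amplitude or acrophase.

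**The concern.** If melatonin is high mainly during sleep, the sampled window catches only the edges of the secretion pulse. The highest observed value is then either the bedtime or the awakening sample, and the night part of the cosine is extrapolated from the day and those two edges. How far up the rising edge the last sample falls depends on bedtime.

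The study compares groups that are expected to differ in sleep timing, so the measurement window differs by exposure group. Anchoring time to sleep offset aligns the start of the window but does not correct for when sampling stops. A significant difference in melatonin peak or amplitude could then reflect bedtime, altered secretion or both, and a real difference could be masked. This is more than an operational detail for an analysis plan, because the article itself fixes comparisons that its schedule does not observe.

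**Working it through.** **1. The plan's own count.** With 17 h awake the caption gives samples at 0, 6, 12, 14, 16 and 17 h after waking (the 16 h sample is both the two-hourly one and the one an hour before bed). That is six per day, as stated. The gap is 24 − 17 = 7 h. With 15, 16 and 18 h awake the counts are 5, 6 and 7, and the gaps 9, 8 and 6 h.

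**2. Assumed curve.** The article gives no hormone values, so the shape is an assumption. With L(x) = 1/(1 + e^(−x)) and t in hours after waking (the waking sample is t = 24):

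y(t) = 1 + 20 · L((t − r)/0.6) · L((r + 8 − t)/0.6)

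The baseline is 1, the plateau about 21, the pulse lasts 8 h and r is the half-rise. For r = 16: at 16 h, 1 + 20 × 0.5 = 11.0; at 18 h, 1 + 20 × 0.966 = 20.3; at waking (half-fall at 24 h), 1 + 20 × 0.5 = 11.0.

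**3. Move only bedtime.** Fit M + A·cos(2π(t − φ)/24) by least squares, with secretion identical within each value of r.

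| r | Bedtime | Sampled values | Peak | Peak − trough | A | φ |
|---|---|---|---|---|---|---|
| 16 | 16 h | 11.0, 1.0, 1.0, 1.7, 4.2, 11.0 | 11.0 | 10.0 | 7.9 | 21.1 |
| 16 | 18 h | 11.0, 1.0, 1.0, 1.7, 11.0, 17.8, 20.3 | 20.3 | 19.3 | 11.7 | 20.4 |
| 16 | dense | – | about 21 | about 20 | 10.6 | 20.0 |
| 17 | 16 h | 17.8, 1.0, 1.0, 1.1, 1.7, 4.2 | 17.8 | 16.8 | 9.9 | 22.5 |
| 17 | 18 h | 17.8, 1.0, 1.0, 1.1, 4.2, 11.0, 17.8 | 17.8 | 16.8 | 11.8 | 21.9 |
| 17 | dense | – | about 21 | about 20 | 10.6 | 21.0 |

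With r = 16, amplitude rises by 11.7/7.9 − 1 = 48%. With r = 17 the awakening sample is never exceeded, so the peak does not move, and amplitude rises by 11.8/9.9 − 1 = 19%.

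**4. A wider set of curves.** Waking at 07:00, baseline 1, height +30, 8 h pulse, half-rise at 22:00, 23:00 or 24:00, three steepnesses (0.5, 0.75 and 1.25 h), bedtime moved from 22:00 to 01:00:

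- Half-rise 22:00 or 23:00: the observed maximum goes from 52–56% to 90–100% of the true peak; amplitude rises by 36–146%. In the middle case (23:00, 0.75 h) the maximum goes from 52% to 95%, amplitude from 10.2 to 16.8 (dense 15.5), and acrophase from about 4.4 to 3.4 h clock time (dense 3.0).
- Half-rise 24:00: the observed maximum stays at 75–89% whatever the bedtime; amplitude rises by 9–14%.

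**5. Direction.** In that middle case with bedtime held at 01:00, moving waking from 07:00 to 09:00 lowers amplitude from 16.8 to 14.9, because the awakening sample falls later on the declining edge. Later sleep onset and longer sleep can thus pull in opposite directions.

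**6. Cortisol, for contrast.** Under an assumed curve peaking about 0.6 h after waking, with 15 to 18 h awake: observed peak 13.1 at every bedtime (true maximum 17.3), peak-to-trough 11.1 to 11.3, cosinor amplitude 5.86 to 5.07, acrophase about 1.9 h later, slope 0.74 to 0.63 per hour.

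**The case against.** **These are secondary outcomes, and an interpretable melatonin marker is already planned.** This stands. DLMO needs no night sample, and the article says openly that saliva times were a compromise. It limits the severity but does not remove the point, since the unsampled night is not among the limits named.

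**A cosinor does not need samples all round the clock.** This is partly right. If the rhythm were an exact 24-hour cosine, the waking schedule would recover mesor, amplitude and acrophase without bias, with a standard error for amplitude 1.2 to 1.4 times that of evenly spaced sampling. The bias comes from a pulse-shaped profile, which is an assumption here.

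**A reader might infer that the results track bedtime instead of secretion.** That is too absolute. The measures mix the two, and with a late rise the observed peak does not respond to bedtime at all. Nor would it be fair to illustrate the size by delaying onset with the morning fall held fixed: going from 15.5 to 17.5 h shortens secretion from 8 to 6 h, and the densely sampled amplitude itself falls from 10.6 to 8.7. Shifting the whole 8 h pulse across that range (half-rise 15.5, 16.5, 17.5 h; bedtime 17 h) leaves the fitted amplitude at 10.3, 10.4 and 10.3.

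**A reader might extend the point to the cortisol peak.** The documents do not support this. Under the assumed curve that peak is the awakening value and does not depend on bedtime. The missing first-hour samples are a disclosed choice. What remains is labelling.

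**A reader might infer a DLMO baseline that changes with the season.** This needs a sunrise-to-sunset reading of a sentence that simply contrasts evening with daytime samples, plus an assumed latitude and waking time. Three of the four groups are also matched on time of year. Whether the awakening sample counts is unstated, not wrongly stated, and thresholds are commonly left to the analysis plan.

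**Conclusion.** The point holds for melatonin peak, peak-to-trough and cosinor amplitude and acrophase. As scheduled, the first two are extremes of waking samples, and the last two rest on extrapolation across roughly 7 h in the protocol's example. Because sleep timing is expected to differ by group, between-group comparisons of these quantities can show or hide differences with secretion unchanged.

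The size is not fixed by the documents. Under the assumed curves, a two-hour change in bedtime moves the observed peak by anything from nothing (17.8 to 17.8) to a near doubling (11.0 to 20.3), and the fitted amplitude by about 19% to 48%. The three-hour range in the wider set spans 9% to 146% in amplitude. All of this rests on a pulse-shaped profile that is high during sleep, and on a sleep-timing difference whose size the article does not state. The sign of any group bias cannot be predicted.

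For cortisol the conclusion is limited to wording. Severity is moderate: secondary outcomes, with a remedy confined to the analysis text.

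**What to change.** In the Statistical analyses section:

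- Make DLMO, already planned, the main melatonin outcome, supported by evening melatonin concentrations at fixed hours before bedtime.
- Mark melatonin cosinor amplitude and acrophase as exploratory.
- Relabel melatonin peak and peak-to-trough as highest waking value and waking range, and report them with wake duration and time of last sample by group.
- Define the DLMO baseline by hours since waking: the +6 h samples of both days, excluding the awakening sample. This replaces the daylight wording. It matters because an awakening sample may carry night melatonin: in the r = 16 curve, averaging it with the +6 h value gives (11.0 + 1.0)/2 = 6.0 instead of 1.0.
- For cortisol, relabel peak as awakening value and rely on the planned wake-to-bed slope, shown with wake duration because the slope also varies with it.

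In Strength and limitations, add one sentence naming the unsampled night as a limit on melatonin peak, amplitude and acrophase.

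Cost: some listed secondary parameters become exploratory. No samples, visits or assays are added.

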**Fig 2 pone.0306408.g002:**
[figure not shown]
The tridirectional relationship between circadian disturbances, mental disease and obesity. Circadian disturbances, mental disease and obesity are associated through a complex network of intermediating factors, each potentially influencing or being influenced by other factors in the network.

Circadian rhythms in humans can be evaluated through various biomarkers, including hormonal peak values and rhythms, daily body temperature changes, and rhythmic gene expression [26]. Since circadian rhythms are closely intertwined with daily routines, measurements taken in laboratories or in-hospital settings may have low ecological validity due to the impact of these artificial environments. Therefore, there is a need for minimally invasive sampling techniques, compatible with daily routines, which can be applied in a real-life setting.

The primary aims of this study are to: (i) To investigate biological markers of disturbed circadian rhythm in free-living adults with obesity and schizophrenia or BD using non-invasive methods and; (ii) to compare biological markers of disturbed circadian rhythm with subjective and objective measures of sleep quality.

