Significant findings from the correlational matrices will be further evaluated by longitudinal analyses (e.g. linear regression). In these analyses, measures of circadian rhythmicity e.g., acrophase of clock gene expression, will be used as dependent variables. Independent variables will be ‘group allocation’, BMI, gender and age. Variables with an insignificant effect will be skipped from the model. Subsequently, other variables with a potentially confounding influence as identified in the correlational matrix will be added to the model. The most appropriate model will be selected based on the Akaike Information Criterion (AIC), with preference given to the model having the lowest AIC score [32].

In all tests, a p-value below 0.05 is considered significant.

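### Clock-gene/sleep associations are screened by correlations not adjusted for study group, so associations that run against the group difference can be lost before the regression

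*Protocol article*

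**What the plan says.** The Background section of the protocol article closes with two primary aims, the second being "to compare biological markers of disturbed circadian rhythm with subjective and objective measures of sleep quality". Under Statistical analyses, this aim is served in two steps.

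- **Step 1, correlation.** "The correlation between clock gene expression and sleep parameters" is examined by Spearman's rho: it "will be investigated through Spearman’s rho in correlation matrices". On confounding: "Additional potentially confounding variables will be added to these matrices". The variables meant are then given: "This includes variables related to diet, body composition, medication, physical activity and media device usage". Study group is not in that list, and no partial or stratified correlation is mentioned.
- **Step 2, regression.** "Significant findings from the correlational matrices will be further evaluated by longitudinal analyses (e.g. linear regression". A measure of circadian rhythmicity is the dependent variable. "Independent variables will be ‘group allocation’, BMI, gender and age". Terms without a significant effect are then removed, with no exemption for group. Confounders picked out from the matrix are added, and the model with the lowest AIC is chosen. Significance is p below 0.05 in all tests.

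The same section says that the primary outcome and inter-day variability are analysed for each group. It does not say this of the correlations.

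**The concern.** The sample is four deliberately contrasting groups of 20. The protocol itself expects both sides of the correlation to differ between them. Strength and limitations expects later sleep onset and longer sleep in both psychiatric groups. Table 1 excludes sleep disorders (other than apnoea in the obesity group) and sleep medication from the two non-psychiatric groups, but only oral melatonin use from the psychiatric groups. The power calculation is built on group differences in clock-gene expression.

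A correlation across all participants then mixes the association within groups with the difference between groups. If the two run the same way, a pair can be flagged with no association inside any group. If they run in opposite directions, a real within-group association can cancel out. Putting a confounder into the matrix shows its own pairwise correlations but removes its influence from none of the others.

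The two errors differ in consequence. A falsely flagged pair meets a regression that starts with group. A pair that fails the screen meets nothing further. At stake is the loss of true findings on a primary aim.

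**Working it through.** **1. Size of clock-gene difference behind the sample size.** The Power calculation section gives 17 per group (mesor) and 16 (amplitude) for an unpaired t-test, power 0.8, alpha 0.05. The effect size is not stated, so the figure can only be solved backwards. By the normal approximation, d = (1.96 + 0.84) × √(2/n):

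- n = 17: 2.80 × √(2/17) = 0.96 (0.99 with the exact two-sided t-test)
- n = 16: 2.80 × √(2/16) = 0.99 (1.02 exact)

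A group shift of about 1 SD in clock-gene expression is therefore the planning value. The documents give no size for the sleep shift, no within-group correlation, and no sample size for the correlations.

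**2. What pooling does, in closed form.** Assume that both psychiatric groups (half the sample) are shifted by d within-group SDs in both variables, with within-group correlation r. The shift adds d²/4 to each variance and ±d²/4 to the covariance, so the pooled Pearson correlation is (r ± d²/4) / (1 + d²/4). With n = 80, significance needs a coefficient of about 1.99/√(78 + 1.99²) = 0.22.

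- r = 0, same direction: d = 0.5 gives 0.0625/1.0625 = 0.06; d = 0.8 gives 0.16/1.16 = 0.14; d = 1.0 gives 0.25/1.25 = 0.20.
- r = 0.3, opposing: d = 0.5 gives 0.2375/1.0625 = 0.22; d = 0.8 gives 0.14/1.16 = 0.12; d = 1.0 gives 0.05/1.25 = 0.04.

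**3. Simulation of the matrix step.** 4 × 20 participants, normal data, two-sided 0.05; pooled Spearman against Spearman with ranks adjusted for group.

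| Assumed situation | d = 0.5 | d = 0.8 | d = 1.0 | Group-adjusted |
|---|---|---|---|---|
| r = 0, same-direction shifts (false positives) | 7–8% | 23% | 45% | about 5% |
| r = 0.3, opposing shifts (passes the screen) | 47% | 15% | 5% | about 70% |
| r = 0.4, opposing shifts (passes the screen) | 78% | 38% | 13% | about 93% |

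With no group shift at all, the pooled screen passes 74% for r = 0.3 and 94% for r = 0.4. Repeat runs agree to within a point or two.

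**4. Simulation of the planned sequence.** Spearman screen; then group, BMI, gender and age; non-significant terms dropped; sleep variable added and tested at 0.05. The BMI and age distributions were assumed, and the final AIC choice was not simulated.

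- *False correlations (r = 0).* Significant at the end in 2.9–4.0% of runs, or 2.4–2.9% if group is always kept. Group was dropped in 2–65% of the runs that passed the screen, mostly when the shifts were small.
- *Masked correlations (r = 0.3, opposing shifts).* Detected at the end in 44%, 14% and 3% at d = 0.5, 0.8 and 1.0, against 76–77% for a group-adjusted regression run without the screen.

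**The case against.** - **Pooling is inferred.** The article never says that all 80 participants enter one matrix, it speaks of matrices in the plural, and it condenses a fuller plan. This stands as a limit on certainty. Pooling is still the more natural reading, because the regression that follows uses group as a covariate. Separate matrices by group would not rescue the screen: with n = 20, Fisher-z power is about Φ(√17 × 0.310 − 1.96) = 25% for r = 0.3 and Φ(√17 × 0.424 − 1.96) = 42% for r = 0.4.
- **The regression corrects false correlations.** This stands. A reader might infer that correlations created by group differences become the trial's conclusions, or that aim (ii) rests on unadjusted correlations alone. The documents do not support either reading: flagged pairs go to a regression that begins with group, and few false ones survive. The rule that lets group be dropped weakens that protection only slightly.
- **Masking needs opposing shifts.** The documents do not predict that direction. With shifts in the same direction the screen passes more often. This stands: the loss is a risk, not a forecast.
- **Phase is individualised.** Cosine analyses are set relative to each participant's measured sleep offset, which plausibly removes part of a shared timing shift in acrophase. It does nothing for mesor or amplitude.
- **An across-group correlation can be of interest.** Aim (ii) does not specify a within-group association, and whether a marker tracks sleep across the healthy-to-ill range is a fair exploratory question. That justifies showing unadjusted coefficients, not using their p-values to decide what is modelled.

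**Conclusion.** The concern holds in a limited form. The two-step rule is stated in the article, so this is not a detail left to an analysis plan. The screen does not adjust for group, its significance decides what reaches the regression, and group is not protected once there.

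False significance at the matrix step ranges from barely inflated at 0.5 SD shifts to nearly one in two at 1 SD. It matters chiefly if matrix p-values are reported as results in their own right. The loss of masked associations is the larger problem, because no later step can recover them; even at 0.5 SD opposing shifts, a correlation of 0.3 passes the screen less than half the time.

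These sizes rest on assumed sleep shifts, assumed within-group correlations, normal data, and the inferred pooling. Only the clock-gene shift of about 1 SD has a basis in the document, through the stated group sizes.

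**What to change.** In Statistical analyses:

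1. Replace the screening correlations by partial Spearman correlations adjusted for study group (ranks of both variables taken as residuals on group indicators), with age and gender added if wanted. State that all 80 participants are used.
2. Show the within-group coefficients as description only; with 20 per group they are imprecise. Unadjusted correlations may also be shown as description.
3. Do not let unadjusted significance decide which pairs go to regression. Use the group-adjusted coefficients, or name the pairs to be modelled in advance.
4. Keep group in every regression model whatever its p-value, and exempt it from the removal rule and the AIC choice.

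Cost: three degrees of freedom for group, five if age and gender are added, and a little more analysis on data already being collected. Where the groups do not differ, the loss of power is small: for r = 0.3, about 70% adjusted against 74% pooled.

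### Aim (ii): regression is run only on pairs already significant in an unadjusted matrix from the same 80 people, so it is not independent support for a picked pair and can miss masked associations

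*Protocol article*

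**What the plan says.** The second primary aim, given at the end of the Background section, is "to compare biological markers of disturbed circadian rhythm with subjective and objective measures of sleep quality". The Statistical analyses section sets out how it is pursued:

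- **Screen.** The relation between clock gene expression and sleep parameters "will be investigated through Spearman’s rho in correlation matrices". The matrix is then widened: "Additional potentially confounding variables will be added to these matrices". These variables cover diet, body composition, medication, physical activity and media device use.
- **Selection.** "Significant findings from the correlational matrices will be further evaluated by longitudinal analyses (e.g. linear regression").
- **Model.** Rhythm measures are the dependent variables. The starting terms are fixed: "Independent variables will be ‘group allocation’, BMI, gender and age". Any of these that fail to reach significance are then taken out. After that pruning, the matrix is used a second time: "Subsequently, other variables with a potentially confounding influence as identified in the correlational matrix will be added to the model". Among the candidate models, the one with the lowest AIC is preferred.
- **Threshold.** "In all tests, a p-value below 0.05 is considered significant".

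There is one sample of 80 (four groups of 20, Methods). For this step the article describes no hold-out or replication sample and no correction for selection, and it does not call the step exploratory.

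**The concern.** A sleep measure reaches the regression because it already correlated at p < 0.05 with the same rhythm measure in the same people. The regression p-value is then read against a null distribution that assumes the predictor was chosen without looking at those data. For a chance correlation, the second result largely repeats the first.

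The screen also works in the other direction. It pools four groups without adjustment. If group or BMI pushes the two variables in opposite directions, a real within-group association can vanish from the pooled Spearman coefficient, and the pair is then never modelled.

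At stake is the answer to a primary aim. A result significant in both the matrix and the adjusted model could be read as two pieces of evidence, and a pair missing from the regressions could be read as a negative finding.

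**Working it through.** The article states no error rate for this two-step route, so there is no figure of its own to reproduce. The check simulates the route.

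**Inputs from the article.** N = 80 in four groups of 20; Spearman screen at p < 0.05; regression on group (3 indicator terms), BMI, gender and age; p < 0.05.

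**Assumptions, not in the article.** Two-sided tests, all 80 pooled, and the distributions and group shifts given below.

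**1. Null pairs, no confounding, normal data (400,000 pairs).**
- Share passing the screen: 5.05%.
- Share of those picked that also pass the regression with all covariates: 62.2%.
- Share of all null pairs passing both steps: 0.0505 × 0.622 = 0.0314, about 3.1%.

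**2. Variations on step 1 (share of picked null pairs that pass).**

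| Setting | Share |
|---|---|
| Non-significant covariates dropped first (the article's rule) | 68.5% |
| No covariates | 71.6% |
| N = 68 / 60 / 40 / 20, all covariates | 59.5% / 58.7% / 56.6% / 50.8% |
| One variable gamma, one normal | 52.6% |
| Both t with 5 df | 48.4% |
| Both gamma | 45.4% |
| One log-normal | 33.8% |
| Both log-normal, untransformed | 17.6% |

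If retention by AIC is used instead of p < 0.05, the variable is kept in 95.0% of picked null pairs in the base case.

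**3. Null within groups, but both variables shifted by group.** The shift is graded evenly across the four groups, in the same direction for both variables, with all covariates in the model.

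| Largest group difference | Share of picked pairs that pass |
|---|---|
| 0.5 SD | 49% |
| 1.0 SD | 14% |
| 1.5 SD | 5% |

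At 1.5 SD the screen picks about 58% of such pairs, and the adjusted regression then rejects about 95% of those.

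**4. Real association masked by group.** The assumed within-group slope is 0.4, with graded group shifts of opposite sign in the two variables.

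| Largest group difference | Adjusted model fitted to every pair | Screen, then regression |
|---|---|---|
| 1.0 SD | 91% detected | 42% detected |
| 1.5 SD | 91% detected | 5% detected |

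**5. Does the screen raise the study-wide false-positive rate?** The number of pairs is not given, so take 24, 36 and 72 independent null pairs as assumed counts. Testing each once at 0.05 without a screen gives 1 − 0.95^m = 71%, 84% and 98%. Requiring both steps gives 1 − (1 − 0.0314)^m = 53%, 68% and 90%. The screen lowers these rates.

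**The case against.** The strongest reply is that the regression has a real purpose. The article expects later sleep onset and longer sleep in the two psychiatric groups (Strength and limitations), and group differences in clock-gene expression are what the study is sized to detect. A pooled Spearman correlation will then often reflect group alone, and adjustment for group is the right way to expose that. Step 3 of the working bears this out, so it would be wrong to say that the regression checks nothing.

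A reader might also infer that about 62% of all null pairs end up as false positives. They do not. The 62% is conditional on having been picked, and per pair the two-step rule is stricter (3.1%) than a single regression at 0.05. Nor should the conditional 62% be divided by the unconditional 5% and quoted as an excess, because the two are not the same kind of rate. Likewise, the chance of at least one false positive across many pairs is multiplicity, not harm from the screen (step 5 of the working).

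The wording is also modest. The article speaks of evaluating findings further, not of confirming them, and it sets no explicit pass rule for the selected pair. It does not spell out that the flagged sleep measure enters as a predictor, though adding variables identified in the matrix implies it. The list of sleep parameters is in S5 File, which is not shown, and multiplicity control and exploratory labelling may be in an analysis plan that is not shown.

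What remains is a rule the article does state: same people, same threshold, and only screened pairs modelled. Adjustment for covariates does not undo selection on a chance correlation, and it cannot recover a pair that was never passed on.

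**Conclusion.** The concern holds in a limited form. For a pair picked by the matrix, the regression is not independent confirmation against chance. Under N = 80, normal data and no group confounding, about 62% of picked null pairs pass it (about 3% of all null pairs pass both steps). The share is about 18% for two heavily skewed untransformed variables, and about 5% where a 1.5 SD group difference drives the correlation. All these figures rest on the assumed distributions and shifts. The coefficient of a picked pair is also not independent evidence; its selection bias was not quantified here.

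The loss of masked associations is the second part of the problem. It can be large under the assumed opposing shifts (91% against 42% or 5% detected), but the article gives no data to say how likely such shifts are.

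The documents do not support the stronger inferences that the screen inflates the study-wide false-positive rate or that the regression is worthless. The between-group comparison of the primary outcome is not affected. The change is worth making because it concerns a stated primary aim and costs little.

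**What to change.** In the Statistical analyses section, separate the regression from the screen:

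- Prespecify a short list of sleep measures and rhythm parameters for aim (ii).
- Fit the model adjusted for group, BMI, gender and age for every listed pair, whatever its Spearman result, and do not drop covariates by significance.
- Report every estimate with its confidence interval and a false-discovery-rate-adjusted p-value over the list.
- Label the remaining matrix, and any model chosen from it by significance or AIC, as hypothesis-generating.

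The cost is a paragraph of wording and a few more regressions on data already being collected. The downside is that fewer findings can be called significant.
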